**2. List the criteria for exclusion**

- Currently participating in exercise training: >30 min. of physical activity per day, >2 days/week)
- Cigarette smoking (presently or in the past 6 months), drug or alcohol abuse
- Pregnancy or breastfeeding
- History of congestive heart failure, ischemic heart disease, severe pulmonary disease.
- History of cancer (within 5 years)
- Diagnosed as insulin-dependent diabetes.
- Change in psychotropic medication dosage in past six weeks
- AST or ALT > 3 times normal range
- Currently involved in any active weight loss treatment program (other than self-directed attempt at calorie restricting diet) or lean patients (BMI <29 kg/m^2^).
- Current purging behavior occurring > once a week over the past six weeks (self-induced vomiting for weight control purposes, laxative or diuretic abuse)
- Revisional bariatric procedures including a RYGB reversal to a SG or a LAGB revision to a SG or RYGB if the band has been adjusted in ≤ 1 year.
- Active psychotic illness, including bipolar affective disorders.
- Evidence of current suicidality or homicidality
- Conditions associated with significant cognitive dysfunction (e.g. dementia) or medical instability that puts the participant at risk
- Contraindication to exercise (severe/uncontrolled CVD; inability to walk 2 blocks, bone or joint problems )
- Allergy to “caine” family drugs (e.g. lidocaine).
- Currently taking active weight suppression medication (e.g. phentermine,bupropion SR, topiramate).
- On medication known to cause substantial weight gain (e.g. atypical antipsychotics such as olanzapine, sodium valproate, steroid therapy). This would not include medications commonly used in this population that usually result in only mild weight loss (e.g. SSRIs).

**3. List any restrictions on use of other drugs or treatments**.

- Medication or food supplement known/thought to affect insulin sensitivity or endothelial function (TZDs, sufonylureas, biguanides, alpha-glucosidase inhibitors, phosphodiesterase inhibitors, beta-blockers, alpha-blockers, ACE-inhibitors, ARB’s, fibrates, glucocorticoids, fish oil, allopurinol, Vitamin E, Vitamin C).
- Subjects cannot ingest medications or food supplements (e.g. statins, dietary supplements, etc.) 24 hours before testing.
- Subjects cannot drink alcohol 24 hours before testing.
- Subjects cannot eat or drink foods that contain caffeine 24 hours before testing.
- Subjects must refrain from any structured exercise for 24 hours prior to testing and limit exercise to their normal everyday activities.
- Currently taking active weight suppression medication (e.g. phentermine,bupropion SR, topiramate)
- On medication known to cause substantial weight gain (e.g. atypical antipsychotics such as olanzapine, sodium valproate, steroid therapy). This would not include medications commonly used in this population that usually result in only mild weight loss (e.g. SSRIs).

# Statistical Considerations

1. **Is stratification/randomization involved?**

No. Subjects will be match paired.

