# Brief Summary/Abstract

Obesity is a major health concern that has been associated with an estimated 2.8 million deaths worldwide each year. The number of individuals considered obese with a Body Mass Index (BMI) above 30 kg/m^2^ has grown to more than 500 million. The increased morbidity and mortality associated with obesity stems from a long list of comorbidities, including hypertension, coronary artery disease, stroke, cancer, and type 2 diabetes (T2D). Bariatric surgery is an emerging intervention that has been used frequently to induce weight loss for obese individuals and it has been shown to improve glycemic control and insulin resistance in people at risk for type 2 diabetes. Beyond weight loss and improved glycemic control, surgery may lead to healthy improvements in inflammation, immune cells and vascular health. It is already known that exercise and weight loss from lifestyle modification can improve glycemic control, insulin resistance, levels of inflammatory cytokines, gut bacteria and arterial stiffness. However, no work has been done to examine a combination of bariatric surgery and pre-surgery lifestyle modification with diet and exercise. Recent work by our team has evidence demonstrating that health status pre-surgery has an impact on post-surgery outcomes. Such findings suggest that improvements in health status from exercise and/or caloric restriction before surgery may improve surgery outcomes as well as surgery-induced health outcomes. To date, no study has systematically examined the role of diet and/or exercise on the prevalence of surgery complications or on post-surgery weight loss, glycemic control, and insulin resistance. Moreover, no work currently exists with lifestyle modification, with or without bariatric surgery on adipose tissue derived inflammation related to immune cells or gut bacteria. Therefore, the purpose of this study is to investigate the effect of pre-surgery lifestyle intervention with diet and/or exercise on bariatric surgery outcomes. To test this objective, subjects will participate in a match paired study, based on BMI. Subjects will undergo testing of blood chemistry and related measures of health before and after lifestyle intervention, as well as 4 weeks post-bariatric surgery. The subjects will be match paired to standard care or exercise until these interventions are filled. Once standard care and exercise interventions are full subjects will then be match paired to exercise plus diet and then diet last. After the intervention all subjects will receive surgery. Post surgery outcomes will be assessed by examining surgery operating time, changes in blood chemistry, adipose tissue biopsies and other measures indicative of glucose and vascular health.

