**►IF YES, explain the kind of controls to be used.**

Subjects will have pre-intervention testing to determine efficacy of exercise and/or diet on insulin sensitivity and immune health.

1. **What is the study design?**

Matched pair, prospective design. Bariatric patients will be match paired to the exercise or standard medical care group. Subjects not undergoing bariatric surgery will be randomized to calorie restriction or calorie restriction + exercise groups.

1. **Does the study involve a placebo?**

No

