# Inclusion/Exclusion Criteria

**1. List the criteria for inclusion**

- Males and Females, 18-70 years of age
- BMI >30 and <70 kg/m^2^
- Sedentary (Not currently participating in exercise training: >30 min. of physical activity per day, >3 days/week)
- HCT for women > 36%, Men >38%
- Non-pregnant (women).-self reported
- Smoker (if bariatric surgery patient) or non-smoker (enrolled for the dietary portion of the study)
- Has the ability/willingness to participate in the study and agree to any of the arms involved in the study.
- No prior surgical procedure for obesity with the exception of a laparoscopic adjustable gastric banding (LAGB) under the condition that the band had not been adjusted in ≥ 1 year

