***Phase 4: Interventions***

Prior to the intervention subject’s undergoing bariatric surgery will be match paired to receive either standard medical care (SC) or exercise + standard care for 4 weeks. Subject’s not undergoing bariatric surgery will then be randomized to the exercise + diet + standard care group or diet + standard care group for 2 weeks.

*Standard medical care:* If subjects are assigned to this group they will not be provided materials to consume healthy diet and increase exercise participation. Subjects will also be asked to participate in the standard education sessions that are provided to all bariatric surgery patients. This standard care includes meetings with a nutritionist, a psychologist, and a bariatric surgeon.

*Diet + standard medical care*: If subject’s are assigned to this group they will be instructed to follow a weight loss diet plan, created for them by the research team. The diet will restrict your caloric intake to 1000-1400 calories per day. Subject’s will be given two meal replacement shakes each day and advice for preparing a standard, calorie-limited dinner designed for weight loss. Subjects are required to pick up food at least 1 time a week. Subjects will return empty bottles of meal shakes to confirm compliance.

*Exercise training* + *standard medical care for bariatric patients*: If subject’s are assigned to this group they will participate in exercise training and the standard medical care outlined above. Subject’s will be asked to exercise 5 days/week. Subject’s will be able to attend regularly supervised and scheduled training sessions with the exercise physiology staff members in Memorial Gym or they can exercise on their own. Overall, the training program will ask subject’s to exercise 5 times per week and 30 min/day. Subject’s heart rate will be monitored continuously during all training sessions, and they will be asked to exercise at an intensity 65-85% of their previously measured HRmax. Walking will be the main type of exercise. In addition to this training program, subject’s will participate in the standard education sessions that are provided to all bariatric surgery patients.

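### The protocol contradicts itself on whether the non-bariatric arms are randomised, and states no chance element for exercise versus standard care in the bariatric cohort

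*Protocol*

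**What the plan says.** **No randomisation.** Statistical Considerations, item 1, asks whether stratification or randomisation is involved. The answer is "No. Subjects will be match paired". The two follow-up fields, for the scheme and for who generates it, are empty.

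**Matched and filled in order.** The Brief Summary/Abstract says that "subjects will participate in a match paired study, based on BMI". It continues: "The subjects will be match paired to standard care or exercise until these interventions are filled". Then: "Once standard care and exercise interventions are full subjects will then be match paired to exercise plus diet and then diet last".

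**Randomised, non-bariatric cohort only.** Study Design: Biomedical says: "Subjects not undergoing bariatric surgery will be randomized to calorie restriction or calorie restriction + exercise groups". Phase 4: Interventions agrees, with subjects "not undergoing bariatric surgery will then be randomized to the exercise + diet + standard care group" or to diet plus standard care. The note under the non-bariatric visit schedule also says randomised.

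**Matched, bariatric cohort.** Study Design says: "Bariatric patients will be match paired to the exercise or standard medical care group". The abstract, Phase 4 and the note under the bariatric schedule agree.

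Two other statements bear on the point. An inclusion criterion requires that the subject "Has the ability/willingness to participate in the study and agree to any of the arms involved in the study". Section 2.5 of the Data and Safety Monitoring Plan records that the study is not masked.

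**The concern.** The primary objectives rest on two contrasts, Ex+CR versus CR and Ex versus standard care (SC), and both are worded as effects of the intervention. How subjects reach their arm decides whether that wording can be defended, and analysis cannot repair it afterwards.

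The two contrasts are exposed in different ways. For Ex+CR versus CR, the text gives two procedures that cannot both be carried out, and one of them separates the arms in time. For Ex versus SC, the text is consistent but incomplete. BMI decides who is paired with whom, and nothing stated decides which member of the pair exercises. If staff who know the patients make that choice, differences in fitness, glycaemic status or motivation could be read as an effect of exercise. Several outcomes depend on effort or self-report, such as the maximal exercise test, the six-minute walk and quality of life.

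**Working it through.** **1. Passages side by side.**

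| Place in the protocol | Bariatric arms (Ex, SC) | Non-bariatric arms (Ex+CR, CR) |
| --- | --- | --- |
| Statistical Considerations, item 1 | matched, not randomised | matched, not randomised |
| Brief Summary/Abstract | matched on BMI, filled together, first | matched on BMI, Ex+CR next, CR last |
| Study Design: Biomedical | matched | randomised |
| Phase 4: Interventions | matched | randomised |
| Visit schedule notes | matched | randomised |

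The conflict has two sides and lies in the right-hand column. The first two rows agree that no one is randomised; the other three randomise the non-bariatric cohort. Filling CR after Ex+CR also prevents a matched pair from being split concurrently between those two arms.

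**2. How far apart the arms would be if the abstract is followed.** Months to fill an arm = 12 × arm size / enrolments per year, assuming all enrolment goes to the open arm. The arm size is 14 (sample size justification). The timeline item under Human Participants supports two rates that disagree:

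- Stated rate of 8-12 a year: 12 × 14/12 = 14 months; 12 × 14/8 = 21 months.
- Rate implied by 60 subjects in 18-36 months: 60/3 = 20 to 60/1.5 = 40 a year, so 12 × 14/40 = 4.2 months to 12 × 14/20 = 8.4 months.

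The rates disagree because 8-12 a year over 1.5-3 years gives 12-36 subjects, not 60. Both count enrolled subjects, whereas the 14 are treated. With 50 treated of 60 enrolled, as the protocol expects, each duration lengthens by 60/50 = 1.2. At either rate the two recruitment periods do not overlap.

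**3. What a calendar shift would do (illustration only).** The protocol gives no figure for drift, so the shift s between the two periods, in SD units, is assumed. For a two-sided 5% two-sample t-test with n per arm and no true effect, the rejection rate comes from the noncentral t distribution with 2n − 2 degrees of freedom and noncentrality s × √(n/2).

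| Assumed shift | 14 per arm | 12 completers per arm |
| --- | --- | --- |
| 0.25 SD | 10% | 9% |
| 0.50 SD | 25% | 22% |
| 0.75 SD | 48% | 42% |

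If the arms are randomised concurrently, this inflation does not arise.

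**4. Ex versus SC.** Human Participants, item 2, expects 16 treated and 12 completing bariatric subjects: 16/2 = 8 and 12/2 = 6 per arm. BMI is the only matching variable named. No section gives a chance mechanism or concealment for these arms, and item 1 of Statistical Considerations rules randomisation out. In groups of 6-8, matching on BMI cannot be relied on to balance other prognostic factors.

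**The case against.** The abstract may be leftover text. It also says that all subjects go on to surgery, which does not fit a design with a non-surgical cohort. The design section, Phase 4 and the schedule note all point to a coherent hybrid: matched bariatric patients and randomised non-bariatric subjects. This stands to the extent that a reader might infer that Ex+CR versus CR is confounded with time in any event, and the document does not support that. The confounding is conditional on the abstract. But the abstract is current text, and the answer in the statistical section excludes the hybrid too.

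A reader might also infer that season threatens both contrasts. It does not threaten Ex versus SC in this way, because even the abstract fills those two arms together.

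For Ex versus SC, matching is a legitimate design and the protocol calls its data preliminary. Every subject must accept any arm, the exclusions remove people who cannot exercise or already do, and the analysis uses change over time. These points limit self-selection by patients and differences in baseline level. They do not limit staff choice, and they do not balance factors that drive response. That staff would steer patients is an inference, since the protocol is silent on how the pair member is chosen. The paragraph on dropout even speaks of treated subjects as randomised without limiting this to one cohort. The silence is the defect; no actual steering is shown.

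**Conclusion.** The contradiction is certain and must be resolved, because staff cannot follow both sets of instructions for the non-bariatric arms. A separation of about 4-8 or 14-21 months per arm, with no concurrent control, follows only if the abstract is followed and all enrolment goes to the open arm. The error rates above rest on an assumed drift and show sensitivity, not an expected bias.

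The weakness in Ex versus SC does not depend on which passage governs. Under every section that describes allocation to these arms they are matched, with BMI the only variable named and no stated chance element or concealment, in an unmasked study with about 6-8 per arm. It is a risk of selection whose size cannot be computed from the protocol.

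A reader might count three mutually incompatible schemes. The text supports two, since the statistical section and the abstract agree that subjects are matched rather than randomised.

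**What to change.** - Change the answer in Statistical Considerations, item 1, to yes, and complete the fields for the scheme and for who generates it.
- Non-bariatric cohort: randomise 1:1, concurrently, to CR or Ex+CR. Blocking on BMI is optional.
- Bariatric cohort: keep the BMI matching, and randomise within each pair or block to Ex or SC from a concealed, computer-generated list. This goes beyond reconciling the text, because it changes a stated design. It is recommended because it keeps the matching and adds the missing chance element.
- Delete the abstract's sentence on filling the arms in order.
- If bariatric allocation stays non-randomised, or enrolment has already taken place, describe Ex versus SC as a non-randomised matched comparison and do not word its results as intervention effects.

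The cost is a short amendment and an allocation list, with no extra subjects or visits. Eligibility already requires subjects to accept any arm.

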**►IF YES, describe the stratification/ randomization scheme.**

**►IF YES, who will generate the randomization scheme?**

_____

**2. What are the statistical considerations for the protocol?**

This study is a between-within subjects repeated measures design in which insulin sensitivity will be measured before and after interventions across 4 experimental conditions. The outcome measures to be assessed are as follows:

**Outcome assessments pertaining to the primary objective:**

- 1. Assess the absolute mean difference in the 3-hr postprandial glucose AUC between the 2 different conditions undergoing bariatric surgery and the 2 different groups not undergoing bariatric surgery.
  2. Assess the absolute mean difference in the 3-hr postprandial insulin AUC between the 2 different groups undergoing bariatric surgery and the 2 different groups not undergoing bariatric surgery.
  3. Compare the postprandial insulin sensitivity across conditions (as measured by the insulin sensitivity index- ISI; a calculated value based on the glucose/insulin values obtained from the MMTT or OGTT)
  4. Compare the mean change in body fat between groups.
  5. Compare the mean change in body weight between groups.
  6. Assess the change in cardiorespiratory fitness between groups.
  7. Determine and compare the immunophenotype from blood between groups.
  8. Relate the insulin sensitivity responses to the immunophenotyping from blood via correlations.
  9. Relate the pulse wave velocity responses to the insulin sensitivity and immunophenotyping under each condition by calculating a 3-hour pulse wave velocity AUC.
  10. Relate the augmentation index responses to the insulin sensitivity and immunophenotyping under each condition by calculating a 3-hour pulse wave velocity AUC.

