**4. What is your plan for primary variable analysis?**

***Analysis between weight loss, insulin sensitivity and immune health:***

Data will be analyzed using R (Vienna, Austria, 2011). A two-way repeated measures analysis of variance (ANOVA) will be used to assess time course differences (group x test) for **AIM 1** and **AIM 2**. A repeated measures ANOVA will also be used to assess differences in adipose cell depot among groups (**AIM 3**). Bonferonni post-hoc analysis will be used to determine group differences and paired t-tests will be used to assess within treatment effects. Linear regression analyses will be used to identify relationships between respective variables. A *P*<0.05 will be considered statistically significant. Data will be expressed as mean ± SEM.

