**5. What is your plan for secondary variable analysis?**

The same statistical approach to primary variable analysis will be conducted.

Bivariate regression analysis to understand the relationship between blood and urine MPs to inform future studies which tissue to collect from. Currently, it is not understood how MPs collected in the blood relate to MPs collected in the urine.

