**Blood draws**:

- In the morning of the 4 study testing days, an IV catheter will be inserted into a vein in either the forearm or the back of the subject’s non-writing hand.
- The IV catheter will be in their arm for the remainder of each visit (about 5 hours), and removed before they leave the CRU.
- During the 4 study visits their blood will be drawn as follows:
  - Fasted
  - Every 30 minutes up to 180 minutes after their drink the beverage
- On each visit, a total of approximately 5-6 tablespoons of blood will be drawn. The blood we take will be tested to measure glucose, insulin, and substances that will help estimate blood glucose control and vessel health.
- A sweet mixed-meal that contains 4 oz of boost meal shake will start the mixed-meal tolerance test (MMTT) for bariatric patients. An oral glucose tolerance test (OGTT) will be given to subjects not undergoing bariatric surgery.
- Non-bariatric patients will have blood drawn (6 ml per draw; 2 draws) to assess blood microparticles, a new biomarker to assess cardiovascular disease risk, at visit 3 and visit 6 (or 18).
- Once the subject drinks the glucose beverage they will return to bed for the remaining blood draws (3-hours)
- When the blood draws are completed they will be fed lunch and discharged to go home.

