**Glucose Metabolism tests (i.e. blood sugar):**

*Mixed-Meal Tolerance Test (MMTT) – for subjects undergoing bariatric surgery*

- The MMTT is used to help determine how quickly sugar is removed from the blood and insulin levels rise. After the blood sample is taken for the fasting blood sugar test, the subject will drink a meal shake. Five more blood draws will be taken at 30, 60, 90, 120, and 180 minutes after they receive the drink. The total amount of blood taken is approximately four teaspoons. During this MMTT, the subjects’ metabolic rate, a measure of the amount of energy it takes to burn calories, will be performed at minutes 0, 60, 120 and 180. During this metabolism measure, subjects will wear a canopy that is connected to a special device (metabolic cart) that measures subjects’ exhaled carbon dioxide (CO_2_) and oxygen. These measurements are then used to calculate the amount of calories they burn and will be performed by trained exercise physiologists.

*Oral Glucose Tolerance Test (OGTT) – for subjects not undergoing bariatric surgery*

- The OGTT is used to help determine how quickly sugar is removed from the blood. After the blood sample is taken for the fasting blood sugar test, they will drink a sugary solution.  Five more blood draws will be taken at 30, 60, 90, 120, and 180 minutes after they receive the drink. The total amount of blood taken is approximately 1 1/3 tablespoons. During the OGTT test, the subjects’ metabolic rate, a measure of the amount of energy it takes to burn calories, will be performed at minutes 0, 60, 120 and 180. During this metabolism measure, subjects will wear a canopy that is connected to a special device (metabolic cart) that measures subjects’ exhaled carbon dioxide (CO_2_) and oxygen. These measurements are then used to calculate the amount of calories they burn and will be performed by trained exercise physiologists. The subject’s appetite response to the OGTT will be tested before and after this test.

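### Two analysis definitions under the primary objective are wrong or contradictory as written: the augmentation index summary and the glucose/insulin sampling times; the ten listed outcomes are also unranked

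*Protocol*

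**What the plan says.** Protocol, Statistical Considerations, item 2, gives a list headed "Outcome assessments pertaining to the primary objective". It has ten numbered items and no order of priority. Items 1 to 7 are comparisons: 3-hour glucose AUC, 3-hour insulin AUC, the insulin sensitivity index, body fat, body weight, fitness and blood immunophenotype. Items 8 to 10 are associations.

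- **Augmentation index.** Item 9 relates pulse wave velocity to insulin sensitivity and immunophenotype through a 3-hour pulse wave velocity AUC. Item 10 is to "Relate the augmentation index responses to the insulin sensitivity and immunophenotyping under each condition by calculating a 3-hour pulse wave velocity AUC".
- **Sampling times.** Under Study Testing Visits 3-6, Blood draws asks for a fasting sample and then "Every 30 minutes up to 180 minutes after their drink the beverage". The next section, Glucose Metabolism tests, says "Five more blood draws will be taken at 30, 60, 90, 120, and 180 minutes after they receive the drink". It uses that same sentence for the mixed-meal test and the oral glucose test.
- **Error control.** Item 4 of Statistical Considerations states that P "<0.05 will be considered statistically significant" and that "Bonferonni post-hoc analysis will be used to determine group differences". For secondary variables, item 5 says "The same statistical approach to primary variable analysis will be conducted".
- **Lead variable.** The design sentence in item 2 says that "insulin sensitivity will be measured before and after interventions across 4 experimental conditions", but insulin sensitivity is not designated as the primary endpoint. Item 3 sizes the bariatric groups on insulin resistance and the non-bariatric groups on a weight difference in kg.

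**The concern.** An outcome definition should lead two analysts to the same number. Two of the definitions here do not.

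Item 10 names one vascular measure and prescribes the summary of another. The Vascular tests section describes augmentation index (characteristics of the pulse waveform) and pulse wave velocity (carotid-to-femoral timing) as separate measurements, so one AUC cannot stand for the other. An analyst must either repeat item 9 or depart from the text.

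The glucose and insulin AUCs are the first two items on the list, and their last hour rests on two incompatible schedules. The insulin sensitivity index is calculated from the same tests.

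The list also leaves open which of the ten results answers the primary objective, and nothing in the protocol limits the error rate across them.

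**Working it through.** The protocol gives no figure of its own on any of these points, so there is none to reproduce.

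**1. Item 10 against item 9**

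| Item | Response named | Summary prescribed |
|---|---|---|
| 9 | Pulse wave velocity | 3-hour pulse wave velocity AUC |
| 10 | Augmentation index | 3-hour pulse wave velocity AUC |

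The response changes between the rows and the summary does not. The likely explanation is a phrase carried over from item 9.

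**2. The two sampling schedules**

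- Blood draws: 0, 30, 60, 90, 120, 150, 180 minutes (six post-drink draws).
- Glucose Metabolism tests: 0, 30, 60, 90, 120, 180 minutes (five post-drink draws), for both tests.

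The schedules agree up to 120 minutes. Write G for the concentration at each time and apply the trapezoid rule from 120 to 180 minutes.

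- Without 150: 60 × (G120 + G180)/2 = 30·G120 + 30·G180.
- With 150: 30 × (G120 + G150)/2 + 30 × (G150 + G180)/2 = 15·G120 + 30·G150 + 15·G180.
- Difference: 30·G150 − 15·G120 − 15·G180 = 30 × [G150 − (G120 + G180)/2].

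The protocol gives no expected curve, so the glucose deviation at 150 minutes is an assumption. The last column also assumes a mean glucose of 120 mg/dl over the window, which gives a total AUC of 120 × 180 = 21,600 mg/dl × min.

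| Assumed deviation at 150 min | Change in AUC (mg/dl × min) | Share of 21,600 |
|---|---|---|
| 5 mg/dl | 30 × 5 = 150 | 0.7% |
| 10 mg/dl | 30 × 10 = 300 | 1.4% |
| 20 mg/dl | 30 × 20 = 600 | 2.8% |

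The same formula applies to insulin, where the relative change could be larger, but the protocol gives nothing from which to size it. The formula for the insulin sensitivity index is not stated. It is affected only if it uses samples taken after 120 minutes.

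**3. False positives across the list**

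Inputs: ten items, of which seven are comparisons; 0.05 per test, taken as two-sided because the protocol does not say. If the tests are independent and every null hypothesis is true:

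- Ten items: 1 − 0.95^10 = 0.401.
- Items 1 to 7: 1 − 0.95^7 = 0.302.

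The outcomes are related: items 1 to 3 share blood samples, and items 4 and 5 are body fat and body weight. The protocol gives no correlations. With an assumed common correlation between test statistics:

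| Common correlation (assumed) | Ten items | Items 1 to 7 |
|---|---|---|
| 0 | 40% | 30% |
| 0.3 | 35% | 27% |
| 0.5 | 29% | 23% |
| 0.7 | 21% | 18% |

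At perfect correlation the figure falls to 5%. These counts take each item as one test.

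**The case against.** **On augmentation index.** A reader might infer that it is never analysed. That goes too far. Item 10 names it as the response, the Vascular tests section measures it, both visit schedules include it, and Specimen Banking at UVa uses it as the in vivo comparator for the vessel work. What is wrong is the summary measure, in one phrase.

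**On sampling.** Blood draws is a general description and Glucose Metabolism tests lists explicit times, so staff may simply follow the explicit list. A reader might also infer that the data will mix the two schedules, or that the mixed-meal and oral glucose tests differ in their times. The text supports neither: nothing assigns different schedules to different subjects or visits, and the two tests share one list. For glucose, the effect under the assumptions shown is also modest. What stands is that two sections specify different samples for the same outcome.

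**On multiplicity.** A reader might infer ten co-primary endpoints with a 40% false-positive rate, any one of which would meet the objective. The protocol states no such success rule. The 40% needs ten independent tests, and three of the items are associations. The sample size section calls the data preliminary work for future power analyses, and error control across outcomes may be set out in a statistical analysis plan that is not at hand. This objection largely succeeds and makes multiplicity the secondary part of the point. Still, the protocol itself leaves its list unranked, and its sample size section makes 80% power statements at an alpha of 0.05.

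**Conclusion.** The point holds as two definite textual defects and one secondary observation.

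- Item 10 prescribes the wrong summary. Read literally, it repeats item 9's measure and yields no augmentation index summary.
- The sampling sections contradict each other at 150 minutes. Items 1 and 2 are affected, and item 3 potentially. The AUC difference is exactly 30 × (150-minute value minus the mean of its neighbours). Its size, 150 to 600 mg/dl × min for glucose, rests on assumed deviations of 5 to 20 mg/dl.
- The ten outcomes are unranked, and the Bonferroni step covers group differences only. The chance of at least one false positive is at most about 40% under independence (30% for items 1 to 7). It is lower under positive correlation, by an amount the protocol does not allow one to fix. This is a gap in stated priorities and does not show that the trial will claim success on any single result.

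**What to change.** 1. In item 10, replace the pulse wave velocity AUC with a 3-hour augmentation index AUC. The Vascular tests section gives repeat times for blood pressure and flow-mediated dilation but none for augmentation index or pulse wave velocity, so state the times that both AUCs will use.
2. Reconcile Blood draws with Glucose Metabolism tests so that one list of times applies. Compute the AUCs and the insulin sensitivity index only from time points common to all subjects and visits.
3. Either designate a lead outcome or state that the ten results are not individually confirmatory. Naming the insulin sensitivity index for everyone is more than a wording change. It matches the basis on which the bariatric groups were sized, but the non-bariatric groups were sized on weight loss in kg and would have no sample size justification for it. The choice should be made with that in view, for example separately for each cohort.

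The first two changes are wording and add no subjects or visits. The third is also wording if the results are declared not individually confirmatory. If one lead outcome is named for both cohorts, the non-bariatric sample size needs a new justification.
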